## **PROTECTION OF PRIVACY AND CONFIDENTIALITY**

**Privacy of individual:** Examinations will take place in a private room. Individual data will be reported to the participants and to relevant staff members, and will be recorded in case reporting forms.

**Confidentiality of data:** All screening forms and case record forms will be kept in a secured location with access limited to authorized staff members. Unique numerical identifiers will be used for the computer-based data entry and blood samples. Publications will contain only aggregate data. No identifying information will be included.

## **EXTRA COSTS TO PARTICIPANTS**

Participants will not incur extra costs through their participation in this study. All examinations, laboratory testing, and medications will be provided free. Participants will be reimbursed for their travel costs. Their participation in the study will require additional visits, so there will be an extra time cost associated with participation.

### **REIMBURSEMENTS OR INCENTIVES**

Patients will be reimbursed 35 Ethiopian Birr (50 Birr those children age>6 years accompanied by a parent) per visit for their travel expenses only to minimize loss to follow-up and to prevent patients from incurring extra expenses in travel to and from the clinic for the purpose of participating in the study. The travel reimbursement will be given to each participant even if they are in the same family.

### **DISSEMINATION, NOTIFICATION AND REPORTING OF RESULTS**

#### **Clinical trial registration**

The clinical trial registration will be done by the investigators through the website [www.clinicaltrials.gov](http://www.clinicaltrials.gov).

#### **Notifying participants of their individual results**

Participants and their parents will be informed of the results of the malaria smear, hemoglobin level, G6PD status, and clinical assessments at the time of enrollment and at each follow-up visit. Filter paper analysis will be completed only after the study is completed at a reference laboratory. Participants will not be informed of their individual results from these tests.

**Notifying participants of findings:** Participants will not be directly notified of the study findings.

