*P. vivax* unlike *P. falciparum* has a dormant stage [hypnozoites] that can persist in the liver and cause relapses by invading the bloodstream weeks, or even years later. Both CQ and AL treat only the *P. vivax* blood stage parasites, resulting in a short-term clinical cure, but these medicines do not eliminate the liver stage infection, leaving the patient at risk of later malaria illness relapses. In a study conducted in Ethiopia in 2009, CQ and AL treatments both caused clinical cures of *P. vivax* malaria lasting up to three weeks in all patients; however, unacceptably high rates of recurrent *P. vivax* parasitemia were noted at 42 days of follow-up, with 41.6% (47/113) in the AL arm and 34% (34/107) in the CQ arm (unpublished data). Many of these recurrent malaria parasitemias were likely caused by relapses of dormant infections, although some probably were from new *P. vivax* re-infections. *P. vivax* infection is ideally treated with either CQ or AL resulting in a clinical cure, then with primaquine (PQ) resulting in a radical cure by eliminating the dormant liver hypnozoite forms. Primaquine radical cure is the standard of care in malaria-free areas such as the United States to prevent relapses and primaquine is the recommended WHO policy for adequate Pv treatment [2].

One study assessing the efficacy of CQ vs. AL both given with primaquine noted cure rates of 97.4% for AL vs. 100% for CQ at day 28 in Thailand [31]. In Ethiopia, the addition of primaquine to CQ decreased the cumulative incidence of therapeutic failure at day 28 by a life-table analysis method from 5.76% to 0.75% and the cumulative risk of relapse at day 157 by a life-table method from 61.8% to 26.3% [32].

Primaquine was previously widely used in Ethiopia according to national malaria treatment guidelines until the late 1990's. However, due to G6PD-related safety concerns that were mostly reported in other countries, primaquine use is now limited to Ethiopian health facilities with good laboratory capacity in non-malarious areas typically located above 2000m altitude. There is currently limited G6PD testing capacity in Ethiopia. The Ethiopian national malaria program is very interested in gathering credible evidence to support the scale up and safe deployment of primaquine for *P. vivax* treatment as the country moves towards malaria elimination.

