- **Primaquine:** 0.25 mg/kg daily for 14 days will be administered on days 2-16 to those with a confirmed normal G6PD test by NADPH fluorescent spot test, which is the most commonly used test and is currently recommended by the International Committee for Standardization in Hematology.

| Body weight (kg)   | mg                 | Number of 15mg tablets |
|--------------------|--------------------|------------------------|
|                    | based on 0.25mg/kg | PER DAY FOR 14 DAYS    |
| 5-14               | 1.25 to 3.5        | ¼                      |
| 15-24              | 3.75 to 6          | ¼                      |
| 25-34              | 6.25 to 8.5        | ½                      |
| 35 -60
And more | 8.75 to 15         | 1                      |

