## **Intervention or treatment**

**Antimalarial Therapy-** All patients will be randomized to receive AL or CQ. Once G6PD results are available, those testing normal will be randomized to PQ or no PQ.. In Ethiopia G6PD deficiency is very rare (0.5-2.9%) [38]. All doses of CQ, PQ, and morning AL will be given under supervision by the staff. The evening dose of AL will be given to the patients to take at home. Children less than 5 years of age will be given an extra evening dose in case of vomiting. Patients will be observed for 60 minutes after treatment for adverse reactions or vomiting. Those patients vomiting their medication within the first 30 minutes will receive a repeat full dose, those vomiting from 30-60 minutes will receive half dose. This is standard practice for anti-malarial treatment.

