9. **Molecular testing.** A filter paper blood spot will be collected on days 0 and after day 3 in case of recurrent parasitemia for an array of parasite molecular testing including genotyping, resistance drug markers, parasite genome sequencing, and for gametocytes. In *P. falciparum* malaria primaquine accelerates clearance of gametocytes and artemisinin derivatives prevent gametocyte development. However, in *P. vivax* malaria effect of these drugs on gametocyte carriage remains unclear due to limited studies. Therefore, we will examine gametocytemia by blood smear and measuring Pvs25 using reverse –transcript quantitative PCR tool in the smear positive DBS from day 0 and follow up visits. Lastly, for any patients noted to have G6PD deficiency or a greater than 2.4g/dL drop in hemoglobin, their DBS sample will be tested for genetic variants of G6PD deficiency. The molecular testing will be conducted in Addis Ababa, Ethiopia, by Ethiopia Health and Nutrition Research Institute (EHNRI). If EHNRI cannot accomplish this in a timely manner, CDC Atlanta, will serve as a back-stop institution. All samples will have the study ID number and date of collection, but no other personal identifiers. The logbook that links the study ID number to the patient will be kept at the study site locked in a cabinet when not in use during the study enrollment period. After the completion of the study, this logbook will be stored in a locked cabinet in Addis Ababa at ICAP’s office. DBSs will not be used for non-malaria-related tests including HIV.

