##### **Adequate clinical and parasitological response**

- absence of parasitaemia on day 28 (day 42), irrespective of axillary temperature, in patients who did not previously meet any of the criteria of early treatment failure, late clinical failure or late parasitological failure

*P. vivax* infections that recur after drug treatment can have 1 of 3 etiologies: 1) recrudescence, 2) reinfection, or 3) relapse arising from the dormant liver stage (hypnozoites). In order to differentiate the recurrent parasitemias as identical vs. different from the original infection, a genotypic analysis will be performed by PCR including characterizing microsatellite markers to assess recrudescence from reinfection and for drug resistance markers. Molecular testing for gametocytes will also be conducted on any smear positive days. Those who fail in the chloroquine arm will have CQ levels tested from the already collected filter paper. Lumefantrine level on day 7 will be measured for those receiving AL treatment from collected filter papers. Patients noted to have G6PD deficiency by the fluorescent spot test and those with hemoglobin drop of >2.4g/dL will undergo additional G6PD genotyping.

**Valid end-points** include treatment failure, completion of the follow-up period without treatment failure, loss to follow-up, withdrawal from study (voluntary or involuntary, and protocol violation). Loss to follow-up occurs when, despite all reasonable effort, an enrolled patient who does not attend the scheduled visits, cannot be found. Patients who withdraw from the study during the treatment period (days 0-2) will be treated with CQ according to the national policy. They will be referred back to the clinic to continue with care.

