## **RISKS**

There is minimal physical and psychological risk associated with this study. The patient may experience a brief moment of physical discomfort and/or fear during the finger prick.

There is minimal risk associated with taking AL, CQ, or PQ. All of the drugs are recommended therapies in Ethiopia, have been widely used, and have been found to be safe (excluding those with G6PD deficiency for PQ). Studies of all of these combinations have reported only mild or moderate adverse events, including dizziness, headache, anorexia, nausea and abdominal pain, noting that these events may also be attributable to malaria. The use of PQ in those without G6PD deficiency is well-tolerated with mild GI discomfort when taken on an empty stomach. The protocol screens for G6PD deficiency, identifying those at hemolytic risk from primaquine therapy, and ensures those that are deficient are not given primaquine.

There are no social risks associated with this protocol. Malaria is a widely recognized disease in Ethiopia, and seeking treatment is socially acceptable. There are no economic risks associated with this study. Patients will be assessed and treated free of charge, and families will be given a stipend of 35 Ethiopian Birr (50Birr for those accompanied by a parent) per visit to cover their travel expenses. Any hospitalization that results from this study or during the follow-up period will be paid for.

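### The rule against returning filter-paper results has no exception for a G6PD-deficient genotype that overturns a normal spot test

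*Protocol*

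**What the plan says.** The protocol section on notifying participants of individual results lists what is returned at enrollment and follow-up visits: smear, hemoglobin, G6PD status and clinical findings. It then turns to filter paper: "Filter paper analysis will be completed only after the study is completed at a reference laboratory". The next sentence is the rule at issue: "Participants will not be informed of their individual results from these tests". No exception follows.

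G6PD genotyping is a filter-paper analysis. Under Laboratory Evaluations, item 9 (molecular testing), patients found deficient or with a hemoglobin drop above 2.4 g/dL are picked out, and "their DBS sample will be tested for genetic variants of G6PD deficiency". The paragraph after the definition of adequate clinical and parasitological response repeats this: "those with hemoglobin drop of >2.4g/dL will undergo additional G6PD genotyping".

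Primaquine is given only "to those with a confirmed normal G6PD test by NADPH fluorescent spot test" (Drugs, dosing of primaquine). Laboratory Evaluations describes that test as qualitative and has it run at the end of each day. The RISKS section says that the protocol screens for deficiency and "ensures those that are deficient are not given primaquine".

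**The concern.** Most of the withheld filter-paper results are parasite genotypes, resistance markers and drug levels. They tell a participant little that bears on later care. The drop-triggered G6PD genotype is different. In a primaquine recipient it can show that the safety information already given to that person was wrong, because everyone who received primaquine had first tested normal. It is also the plan's own check on the assurance given under RISKS.

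At stake is whether that person can avoid primaquine, or ask for testing, in future. The protocol names hemolytic anemia in G6PD deficiency among primaquine's most important harms, though it adds that the commonest African variant usually gives a mild course that resolves by itself. The participant may have few other ways to find out. The Introduction notes that "There is currently limited G6PD testing capacity in Ethiopia", and the paragraph on storage of specimens has samples destroyed once testing is finished.

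**Working it through.** The plan states no figure to reproduce. The check is a reading of the text, followed by arithmetic for scale.

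**Reading**

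1. Primaquine recipients all had a normal spot test (primaquine dosing; Laboratory Evaluations, item 4).
2. A recipient whose hemoglobin falls by more than 2.4 g/dL has the dried blood spot genotyped for G6PD variants (Laboratory Evaluations, item 9; end-points).
3. Dried-blood-spot genotyping is filter-paper work, which the notification section places after the study.
4. The same section says individual results of those tests are not given to participants.
5. The G6PD status that is returned is given at visits, so it is most naturally the same-day spot test and not the later genotype.
6. No other section provides for correcting a status already given.

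Steps 1 to 6 leave a participant with a normal status that the study's own genotype contradicts.

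**Scale**

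Inputs from the protocol:
- 120 patients per treatment (sample size section) and two primaquine arms: 2 × 120 = 240.
- Prevalence d of deficiency: "In Ethiopia G6PD deficiency is very rare (0.5-2.9" percent) (Intervention or treatment).

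Ceiling, if the spot test missed every deficient patient: 240 × d.
- 240 × 0.005 = 1.2
- 240 × 0.029 = 6.96, about 7.0

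The protocol gives no error rate for the spot test. Let f be the share of deficient patients who read as normal, and take specificity as 1. The share of spot-test normals who are deficient is d·f / (1 − d + d·f).

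Assume f = 5% to 20%:
- d = 0.005, f = 0.05: 0.00025 / 0.99525 = 0.000251; × 240 = 0.060
- d = 0.029, f = 0.20: 0.0058 / 0.9768 = 0.005938; × 240 = 1.425

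Assume further that 25% to 75% of these have a drop above 2.4 g/dL:
- low: 0.060 × 0.25 = 0.015
- high: 1.425 × 0.75 = 1.069

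Chance of at least one such participant (Poisson): 1 − exp(−0.015) = 1.5%, up to 1 − exp(−1.069) = 66%.

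The expected number spans about 70-fold (1.069 / 0.015 = 71). About six-fold of that comes from the protocol's own prevalence range and the rest from the two assumed ranges. Excluding patients with a history of hemolysis or severe anemia may lower all of these figures.

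**The case against.** **The rule may be narrower than it reads.** The spot test is described in the same filter-paper item, and Annex V lists G6PD testing with a filter-paper type. It is nevertheless run on the day and its result is returned, so filter-paper analysis in the notification section cannot mean every test done on filter paper. Molecular testing is also planned in Addis Ababa, with a back-up laboratory if it is not timely, which sits awkwardly with a strict after-study rule. This stands as a caution: treating the returned status as the spot test is an inference, though the more natural one. It also means the section does not contradict itself, as a reader might otherwise infer.

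**Other safeguards exist.** Hemoglobin is disclosed, patients are told to return for dark urine, severe side effects needing hospitalization lead to withdrawal, and severe unexpected events go to the ethics board. These reduce the harm, but none of them returns the genotype.

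**The consent form might say something different.** It is not available for this review, so this stays open.

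**Later exposure.** A reader might infer that the participant will probably meet primaquine again because the national programme wants to scale it up. The Introduction does not support that. It reports interest in evidence for scale-up, and says that primaquine is now confined to facilities with good laboratories in non-malarious areas. Participants live in malarious areas.

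**Re-exposure in the trial.** The efficacy end-points section treats each recurrence like the first episode in the randomised arm. A reader might infer that primaquine must be withheld at recurrence after a large drop until a genotype is run on demand. The documents do not carry that far:
- Any such re-exposure would follow from the timing of genotyping, not from the non-return rule.
- How the recurrence rule fits with quinine for treatment failures up to day 42 has to be reconstructed.
- The plan provides no on-demand genotyping.
- Withholding has a cost. If 1% to 5% of 240 had such a drop (assumption), 2.4 to 12 patients would be affected, and the Introduction cites relapse risk at day 157 of 61.8% without primaquine against 26.3% with it.
- It would also change the treatment behind the Phase 2 recurrence comparison.

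That is a debatable trade-off and not part of this point.

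**Conclusion.** The point holds as a small gap in patient safety. The literal rule withholds the one filter-paper result that can show a participant was wrongly cleared for primaquine. It probably affects one participant or none. Only the ceiling of 1.2 to 7.0 among 240 comes from the documents, and it requires a spot test that detects nobody. Everything below it depends on the assumed false-normal rate and the assumed share with a large hemoglobin drop. No estimate, error rate or sample size is touched. The conclusion assumes that the returned G6PD status is the spot test and that the consent form has no contrary provision. The change is worth making because it is cheap, not because the risk is large.

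**What to change.** In the section on notifying participants of individual results, add one exception: if genotyping shows G6PD deficiency in a participant whose spot test was normal, the result is returned to the participant or parent through the study site. The logbook linking study numbers to patients is kept after the study (Laboratory Evaluations, item 9), so the person can be identified. Keep non-disclosure for all other filter-paper tests, and align the consent form if it repeats the rule.

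The cost is one sentence and contact with perhaps one participant after the study. The genotypes are already planned, so no test is added. Timing of the genotyping, treatment of recurrences and the analysis stay as they are.

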#### **Anticipated products or inventions resulting from the study and their use**

All results will be disseminated to the national malaria control programs and other appropriate bodies within the Ethiopian Government including the health centers where the studies will be conducted. We anticipate that the results of this study will be used to inform future changes to the National Malaria Diagnosis and Treatment Guidelines of Ethiopia. In addition, it is anticipated that the evaluators will develop abstracts for presentation at scientific meetings. Finally, one or more detailed manuscripts will be prepared for publication in a peer-reviewed scientific journal.

#### **Disseminating results to public**

The Ethiopian FMOH regularly disseminates key findings to the general public. This occurs through press releases and by including media reporters in data dissemination workshops with local leaders at the conclusion of each major activity, or sooner as important findings become available. Findings from this proposed study that may be of value to the general public can be disseminated through these existing mechanisms.

#### **Scientific Peer Review**

The results from this study will be published in at least one summary paper which will be submitted to a peer-review journal. In addition, additional abstracts may be developed from the results of this study.

#### **Conflicts of Interest**

We have no conflicts of interest.

## ANNEX

### ANNEX I *P. vivax* treatment outcomes

#### For Primaquine:

- Number of vivax episodes following initial parasite clearance during the follow-up period.

#### For artemether-lumefantrine or chloroquine:

##### Early treatment failure

- danger signs or severe malaria on day 1, 2 or 3 in the presence of parasitaemia;
- parasitaemia on day 2 higher than on day 0, irrespective of axillary temperature;
- parasitaemia on day 3 with axillary temperature  $\geq 37.5$  °C;
- parasitaemia on day 3  $\geq 25\%$  of count on day 0.

##### Late treatment failure

##### Late clinical failure

- danger signs or severe malaria in the presence of parasitaemia on any day between day 4 and day 28 (day 42) in patients who did not previously meet any of the criteria of early treatment failure;
- presence of parasitaemia on any day between day 4 and day 28 (day 42) with axillary temperature  $\geq 37.5$  °C (or history of fever) in patients who did not previously meet any of the criteria of early treatment failure

##### Late parasitological failure

- presence of parasitaemia on any day between day 7 and day 28 (day 42) with axillary temperature  $< 37.5$  °C in patients who did not previously meet any of the criteria of early treatment failure or late clinical failure

##### Adequate clinical and parasitological response

- absence of parasitaemia on day 28 (day 42), irrespective of axillary temperature, in patients who did not previously meet any of the criteria of early treatment failure, late clinical failure or late parasitological failure

## ANNEX II Severe malaria definitions

Definition of severe malaria [43]

Severe manifestations of malaria in adults and children

| Prognostic value a  |                  |                                           | Frequency a |        |
|--------------------------------|------------------|-------------------------------------------|------------------------|--------|
| Children                       | Adults           |                                           | Children               | Adults |
| Clinical Manifestations |                  |                                           |                        |        |
| +                              | (?) b | Prostration                               | +++                    | +++    |
| +++                            | +                | Impaired Consciousness                    | +++                    | ++     |
| +++                            | +++              | Respiratory Distress (acidotic breathing) | +++                    | +      |
| +                              | ++               | Multiple convulsions                      | +++                    | +      |
| +++                            | +++              | Circulatory collapse                      | +                      | +      |
| +++                            | +++              | Pulmonary edema                           | +/-                    | +      |
| +++                            | ++               | Abnormal bleeding                         | +/-                    | +      |
| ++                             | +                | Jaundice                                  | +                      | +++    |
| +                              | +                | Hemoglobinuria                            | +/-                    | +      |
| Laboratory findings     |                  |                                           |                        |        |
| +                              | +                | Severe anemia                             | +++                    | +      |
| +++                            | +++              | Hypoglycemia                              | +++                    | ++     |
| +++                            | +++              | Acidosis                                  | +++                    | ++     |
| +++                            | +++              | Hyperlactatemia                           | +++                    | ++     |
| +/-                            | ++               | Hyperparasitemia                          | ++                     | +      |
| ++                             | ++               | Renal Impairment                          | +                      | +++    |

aOn a scale from + to +++; +/- indicates infrequent occurrence

bData not available

